##### Quality of life

(EuroQOL; EQ-5D) [32]. The EQ-5D is a health-related quality of life measure and will be used to generate quality-adjusted life years for use in the economic evaluation. The EQ-5D will be administered before and after treatment, and again at 72 week follow-up.

##### Referrer's assessment of problems

(change in referrer's score on Global Assessment of Functioning; GAF) [33]. The GAF is the standard method for representing a clinician's judgment of a patient's overall level of psychosocial functioning and will be rated by the referrer.

##### Anxiety and depression

(Hospital Anxiety and Depression Scale; HADS) [30]. A reduction in mental distress is an important outcome for service users [17], therefore anxiety and depression will be measured using the 14-item HADS.

##### Client's assessment of problems

(i.e., specific treatment targets for individuals). A focus on the problems most relevant to the client is considered important [34]. Participants will be asked to identify their three most important problems and rate their severity before and after treatment.

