### Study Hypotheses

Our primary hypothesis is that, compared with those in treatment-as-usual, those in PEPS therapy will show a greater improvement in social functioning post-therapy and at follow-up 72 weeks post-randomisation. Secondary hypotheses are that, compared with those in treatment-as-usual, those in PEPS therapy will show the following changes both immediately after therapy and at follow-up: (a) a greater reduction in receipt of unscheduled services; (b) a greater increase in receipt of scheduled services; (c) a greater improvement in quality of life; (d) a greater improvement in referrers' ratings of functioning; (e) a greater reduction in anxiety and depression; and (f) improvement on client-ratings of self-identified three key problems. Regarding intermediate changes, we hypothesise that, compared with those in treatment-as-usual, those in PEPS therapy will show: (a) better therapist alliance after psycho-education; and (b) a greater improvement in social problem solving at end of therapy. We also expect PEPS therapy to show an acceptable level of cost-effectiveness, based on thresholds that appear to guide National Institute for Clinical Excellence (NICE) recommendations.

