##### Receipt and cost of services

(Client Service Receipt Inventory; CSRI [31]). One measure used to capture service use is the CSRI, which records health and social care, criminal justice, informal care services, employment and benefits as reported by the participant. This information will be used in the cost-effectiveness analysis. Service use will be assessed for the period 6 months prior to baseline, and at three points after treatment (immediately after, at 4 months and at 72 weeks). The long-term follow up is necessary to pick up potential improvement overall, rather than capture a temporary increase at the end of treatment.

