### Analyses

Demographic and other baseline data will be summarised by descriptive statistics (number [N], mean, standard deviation [SD], median, minimum and maximum) or frequency tables, stratified by treatment. Measures of adherence to protocol implementation will be summarised by descriptive statistics (number [N], mean, standard deviation [SD], median, minimum and maximum) or frequency tables, stratified by treatment arm. Efficacy will be assessed on the full analysis set, defined as all randomised participants for whom a post-baseline assessment of the primary endpoint is available, that is, in accordance with the "intention to treat" (ITT) principle. The primary efficacy parameter will be the difference in mean SFQ score between treatment arms, estimated using a hierarchical regression model with adjustment for relevant covariates, including centre, sex and personality disorder classification. Differences in mean totals of secondary outcomes at 72 weeks from randomisation will be compared between the two treatment arms, after adjusting for design (centre and sex) covariates. Analyses will be performed using Stata version 11 or above.

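### The stated schedule for the client-rated problems appears to stop at end of treatment, while hypothesis (f) and the named comparison time for secondary outcomes extend to 72 weeks

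*Protocol article*

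**What the plan says.** Three places in the protocol article fix the timing of this outcome.

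- **Study Hypotheses.** Secondary hypotheses (a) to (f) share one opening clause: compared with usual treatment, "those in PEPS therapy will show the following changes both immediately after therapy and at follow-up". Item (f) is "improvement on client-ratings of self-identified three key problems". The primary hypothesis in the same section shows what follow-up means and that it is distinct from the end of therapy: "greater improvement in social functioning post-therapy and at follow-up 72 weeks post-randomisation".
- **Client's assessment of problems.** "Participants will be asked to identify their three most important problems and rate their severity before and after treatment". No 72-week rating is named.
- **Analyses.** The between-arm comparison is described as "Differences in mean totals of secondary outcomes at 72 weeks from randomisation". No end-of-therapy comparison is named for any secondary outcome.

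Two neighbouring paragraphs bear on how the schedule should be read. Quality of life says: "The EQ-5D will be administered before and after treatment, and again at 72 week follow-up". Receipt and cost of services says that service use is assessed "at three points after treatment (immediately after, at 4 months and at 72 weeks".

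**The concern.** The hypothesis needs two post-baseline ratings, one at end of therapy and one at 72 weeks. The outcome paragraph appears to supply only the first, and the analysis section names only the second. If sites follow the outcome paragraph on its natural reading, this outcome has no measurement at its stated comparison time, and the measurement it does have is not assigned to a comparison.

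At stake is whether any gain on the problems that participants chose for themselves lasts. The Background lists the durability of treatment gains as the first gap this trial is meant to fill. For this outcome the question would go unanswered. A later analysis plan could add an end-of-therapy comparison, but it could not recover 72-week ratings that were never taken. The point therefore needs settling while visits are still taking place.

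**Working it through.** No figure in the plan depends on this point, so the check is a comparison of stated time points.

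| Place in the protocol article | Before treatment | End of treatment | 72 weeks |
|---|---|---|---|
| Study Hypotheses, item (f): required | (reference) | yes | yes |
| Client's assessment of problems: collected | yes | yes | not named |
| Analyses, secondary outcomes: compared | n/a | not named | yes |
| Quality of life (EQ-5D), for contrast | yes | yes | yes, as an added point |
| Receipt and cost of services (CSRI), for contrast | yes | yes, plus 4 months | yes, listed as a point after treatment |

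**Step 1: narrow reading.** Suppose that a rating before and after treatment means one rating at each end of the treatment period. The post-baseline times are then:
- required: {end of therapy, 72 weeks}
- collected: {end of therapy}
- compared: {72 weeks}

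Collected and compared have no time in common. Of the two times required by (f), one has data but no named comparison, and the other has a named comparison but no data.

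**Step 2: wide reading.** Suppose that after treatment covers every later assessment, as in the CSRI paragraph. The 72-week rating then exists and the named comparison can be made. What remains is that the text does not say how many ratings are taken, and that no end-of-therapy comparison is named. The latter is equally true of the other secondary outcomes.

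**Step 3: which reading fits better.** The EQ-5D sentence uses the same before-and-after phrase and then adds 72 weeks with a linking word that marks a further occasion. Under the wide reading that addition would be redundant. The CSRI paragraph does use the phrase widely, but it lists the times it means. The record-check paragraph also names 72 weeks. So where this section gives a schedule that reaches 72 weeks, it says so; the client-problem paragraph gives a schedule and does not. The GAF and HADS paragraphs differ in that they give no schedule at all, so the Analyses section can supply their 72-week point without contradiction. The narrow reading is the more natural one, but it is not certain.

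**Step 4: what a 72-week rating would provide.** With 170 recruited per arm and the 30% drop-out assumed under Sample size, 170 × (1 − 0.30) = 119 participants per arm would be expected to give a rating.

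**The case against.** The strongest reply is that the paragraph never says only, and does not exclude a 72-week rating. The CSRI paragraph shows that the authors can use the phrase in a sense that includes 72 weeks. The outcome paragraphs are also plainly not a full visit schedule: GAF and HADS have no times, and the SFQ paragraph names no post-therapy assessment although the primary hypothesis needs one. The schedule may be set out in Figure 2, which is not shown, and an article condenses its full protocol. Analyses names a 72-week comparison without calling it the sole one, and further time points may sit in an analysis plan that is not at hand.

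Most of this stands, and it limits the point. A reader might infer that hypothesis (f) cannot be tested at all, or that its 72-week data are absent by design. The documents support neither. Even on the narrow reading the end-of-therapy half of (f) has ratings and could be tested once that comparison is planned, and the absence of 72-week data rests on an inference about wording. A reader might also infer that the analysis time could be picked after seeing the results. With a single post-baseline rating there would be no choice of time to make, so that argument does not follow.

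What the reply does not remove is that three printed statements about one outcome do not fit together on their natural reading. This is a mismatch between statements, not a detail left out for brevity. If Figure 2 does list a 72-week rating, the outcome paragraph still needs correcting to agree with it.

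**Conclusion.** The point holds in a limited form. On the natural reading of the client-problem paragraph, the follow-up half of secondary hypothesis (f) has no data at the comparison time named in Analyses, and the end-of-therapy ratings have no named comparison. The conclusion assumes that the before-and-after phrase carries the same meaning here as in the EQ-5D sentence, and that Figure 2 does not show otherwise.

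The reach is one of six secondary hypotheses, and for data availability only its follow-up half. The primary outcome, its analysis and the sample size are unaffected. It is worth correcting because the remedy is cheap and a missed rating cannot be recovered later. Confidence is moderate, given the wider usage in the CSRI paragraph and the missing figure.

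**What to change.** Check the schedule in Figure 2 and the case report form, then bring Study Hypotheses, Client's assessment of problems and Analyses into line in one of two ways.

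1. **If the ratings are, or can be, taken at 72 weeks:** state under Client's assessment of problems that the three problems named at baseline are re-rated in both arms at end of treatment and at the existing 72-week assessment. The cost is three extra severity ratings per participant at a contact that is already planned, plus a minor amendment if the rating is new.
2. **If they are not taken at 72 weeks:** limit hypothesis (f) to end of therapy and name that time for this outcome in Analyses. This is a wording change only, but it gives up any statement on whether improvement in the client-rated problems lasts.

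The first option keeps the hypothesis as stated. Neither changes the treatment, the sample size or the primary analysis.

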#### Intermediate outcomes

Two intermediate outcomes are assessed.

##### Treatment alliance

(Working Alliance Inventory; WAI) [35]. The WAI examines the development of treatment alliance, and will be used to assess the effectiveness of the psycho-education component in developing treatment alliance. The WAI is a 36-item questionnaire that can be administered to both clients and therapists. Each item is rated on a 7-point scale and scores are produced on three factors: the therapeutic bond, the agreement on goals, and the agreement on tasks.

##### Social problem solving skills

(Social Problem Solving Inventory-Revised; SPSI-R) [13]. The SPSI-R assesses the development of social problem solving skills to examine whether the social problem solving component improves these skills as expected. The SPSI-R is a 25-item client self-report questionnaire that measures problem solving orientation (positive and negative) and problem solving style (rational, impulsive and avoidant).

#### Process measures

Information will be gathered regarding the route of referral, sessions offered, and participants' attendance. Semi-structured interviews will access information about experiences of therapy, its perceived effects and its perceived limitations. Interviews will also provide an opportunity to support people after psycho-education, since some participants report finding this distressing [36].

A flow chart of the procedures in the PEPS trial is presented in Figure 2.

**Figure 2 F2:**
[figure not shown]
**Procedural Flow Diagram**.

### Analyses

Demographic and other baseline data will be summarised by descriptive statistics (number [N], mean, standard deviation [SD], median, minimum and maximum) or frequency tables, stratified by treatment. Measures of adherence to protocol implementation will be summarised by descriptive statistics (number [N], mean, standard deviation [SD], median, minimum and maximum) or frequency tables, stratified by treatment arm. Efficacy will be assessed on the full analysis set, defined as all randomised participants for whom a post-baseline assessment of the primary endpoint is available, that is, in accordance with the "intention to treat" (ITT) principle. The primary efficacy parameter will be the difference in mean SFQ score between treatment arms, estimated using a hierarchical regression model with adjustment for relevant covariates, including centre, sex and personality disorder classification. Differences in mean totals of secondary outcomes at 72 weeks from randomisation will be compared between the two treatment arms, after adjusting for design (centre and sex) covariates. Analyses will be performed using Stata version 11 or above.

The costs of the interventions will be estimated by combining data on number of sessions provided with unit costs derived from local data on service expenditure and activity. These costs will include therapist time, oncosts, overheads and capital. Costs of other services will be calculated by combining service use data collected with the CSRI with appropriate unit costs. Costs will be compared between the two groups, with bootstrap methods used to generate confidence interval round the difference due to the expected skewed cost distribution. Cost-effectiveness will be assessed by combining the cost adapt with outcomes, namely SFQ scores and Quality-Adjusted Life Years (QALYs). If the costs for the PEPS arm are less than for TAU and the outcome better, then it will be the 'dominant' intervention. However, if costs are greater and outcomes better, then an incremental cost-effectiveness ratio will indicate the extra costs incurred to achieve an extra unit-improvement in outcome (i.e., a one-point improvement on the SFQ or one extra QALY). There will be uncertainty around the point estimates of cost and outcome differences and this uncertainty will be explored by generating a large number of cost-outcome combinations using bootstrapped resample and plotting these on a cost-effectiveness plane. Cost-effectiveness will be interpreted using cost-effectiveness acceptability curves. These will show the probability that PEPS is more cost-effective intervention than TAU for a range of values placed on a unit-improvement in outcome. The range of values for a one-point improvement on the SFQ is unclear, but will be chosen such that we will be able to observe the points at which there is at least at 50% and 80% probability of PEPS being cost-effective. The range of values for a gain of one QALY is more straightforward as it appears that the value that informs NICE recommendations is between £20-30K. Therefore we will use a range of £0-£100K to produce the curve so as to include this threshold.

Thematic analysis methods will be used to specify the nature of treatment-as-usual in terms of what problem was treated by which service/professional and how. Thematic analysis methods will be used to identify themes in participants' opinions of PEPS therapy and TAU.

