### Sample size

The sample size was calculated on the basis of the primary hypothesis. In the exploratory study [22], those referred to PEPS had a greater improvement in social functioning at 6 month follow-up equivalent to 1.05 points on the SFQ. However, a number of people received PEPS who were not included in the trial (e.g., the wait-list control) and, for this larger sample (N = 93), the mean pre-post- treatment difference was 1.79 (pre-treatment mean = 13.85, SD = 4.21; post-treatment mean = 12.06, SD = 4.21). (Note: a lower SFQ score is more desirable). This difference of almost 2 points accords with other evidence that this is a clinically significant and important difference [29]. A reduction of 2 points or more on the SFQ at 1 year follow-up in an RCT of cognitive behaviour therapy in health anxiety was associated with a halving of secondary care appointments (1.24.vs 0.65), a clinically significant reduction in the Hospital Anxiety and Depression Scale (HADS [30]) Anxiety score of 2.5 (9.9 vs 7.45) and a reduction in health anxiety (the main outcome) of 5.6 points (17.8 vs 12.2) (11 is a normal population score and 18 is pathological) [29]. These findings suggest that improvements in social functioning may accrue over 1 year, hence we expect to find a greater magnitude of response at the 72 week follow-up than we did in the exploratory trial. Therefore, we have powered this trial to be able to detect a difference in SFQ score of 2 points. SFQ standard deviations vary between treatment, control, and the wait-list samples, ranging from 3.78 to 4.53. We have based our sample size estimate on the most conservative (i.e., largest) SD. To detect a mean difference in SFQ score of 2 point (SD = 4.53) at 72 weeks with a two-sided significance level of 1% and power of 80% with equal allocation to two arms would require 120 patients in each arm of the trial. To allow for 30% drop out, 170 will be recruited per arm, i.e., 340 in total. We have considered the need to take clustering effects by therapy group into account. In this study, as in the pilot, participants are individually randomised to the treatment arms, and the observed SD of the response in the intervention arm automatically includes the effect of the clustering by therapist. The analysis will take account of this by using a hierarchical model to allow explicit estimation of the between therapy group variance.

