##### Scheduled and unscheduled service use (Record Check)

People with PD are often long-term users of services, but they can be chaotic users of those services. Hence, one valuable outcome would be a more systematic use of the services available. We hope to find a reduction of unscheduled service usage and an increase in scheduled service usage. Data on mental health service use, Emergency Department attendances and hospital admissions will be collected through a review of mental health service and GP records to ascertain use of scheduled and unscheduled services. Service use data will be collected retrospectively for the duration of involvement in the trial, from baseline to 72 week follow-up.

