## Discussion

PEPS therapy has potential as an economical, accessible, and acceptable intervention for people with personality disorder. Individual psychoeducation has the potential to enhance engagement in the group therapy that follows [21,25], thus addressing the important issue of treatment non-completion [19,20]. Problem solving therapy, a major component of PEPS, has a good track record with a range of physical health and mental health problems [14-16], but its effectiveness has not yet been examined with personality disorder. Referring to the PEPS pilot study [22], one commentator noted that the relatively brief PEPS intervention challenges the notion that long-term treatment is always necessary for PD: "The idea that people with personality disorders can only improve after years of treatment has led to a relative neglect of this patient group, based on the belief that they cannot benefit from pragmatic treatment. This study, along with several others, shows that significant progress can be made with less expensive and briefer interventions" [26, p. 121]. There is a recent drive to evaluate briefer interventions for PD [37]. Another commentator noted that, if the PEPS intervention proves cost-effective, then this would "not only improve the evidence base for treatment of personality disorder, but [...] might also go some way towards challenging the ambivalence that some healthcare professionals continue to have about working with people with personality disorders" [25, p. 284]. The PEPS intervention does, therefore, have positive potential in a number of ways.

There are, however, challenges to be met in the course of conducting the trial. We face the potential problem of drop-out between consent to participate and the start of group therapy, since there will be delays caused by waiting for sufficient numbers to accrue in order to start group treatment. This problem will be exacerbated by the intensive nature of the assessment procedure which participants will need to undertake before randomization, hence slowing down the accrual of participants ready for randomization.

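### The efficacy set requires an observed post-baseline SFQ, so it is an available-case (modified ITT) set and not the intention-to-treat set it is called

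*Protocol article*

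**What the plan says.** In the Protocol article, the Analyses section states that efficacy will be assessed on a full analysis set made up of "all randomised participants for whom a post-baseline assessment of the primary endpoint is available". It adds that this is "in accordance with the 'intention to treat' (ITT) principle". The sentence covers efficacy as a whole. The later sentence on secondary outcomes names no other set.

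The Sample size section sizes the trial on the 72-week comparison ("To detect a mean difference in SFQ score of 2 point (SD = 4.53) at 72 weeks") and then inflates for loss: "To allow for 30% drop out, 170 will be recruited per arm, i.e., 340 in total". The 30% is not split by arm or by cause.

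The Study Hypotheses section says that the PEPS arm "will show a greater improvement in social functioning post-therapy and at follow-up 72 weeks post-randomisation". At least two post-baseline SFQ assessments are therefore implied, and the Analyses section does not say which of them admits a participant to the set.

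The Discussion says "We face the potential problem of drop-out between consent to participate and the start of group therapy". It attributes this to the wait for groups to fill, made worse by the length of assessment before randomisation.

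For service use, the Record Check section says that data "will be collected through a review of mental health service and GP records to ascertain use of scheduled and unscheduled services". The Global Assessment of Functioning (GAF) is rated by the referrer.

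**The concern.** Intention-to-treat keeps every randomised participant in the arm to which they were allocated. A set that admits only people who later supply an outcome gives up the protection of randomisation to the extent that supplying it depends on arm and prognosis. The definition and the label therefore disagree within one sentence. The article states this rule outright, so it is not a detail left to an unseen analysis plan.

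Three things are at stake. First, the primary SFQ difference would carry an ITT label while estimating a contrast among responders. Second, because the qualifying SFQ is not named, two analysts could build different sets. Someone with an end-of-therapy score but no 72-week score is in the set on one reading and out on another. Third, read literally, the rule also removes people without an SFQ from the record-check and GAF analyses, although neither measure needs the participant to complete a questionnaire.

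**Working it through.** **1. The plan's own figure.** Inputs from Sample size: difference 2, SD 4.53, two-sided 1%, power 80%, equal allocation.

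n per arm = 2 × (z₀.₉₉₅ + z₀.₈₀)² × SD² / difference² = 2 × (2.576 + 0.842)² × 4.53² / 2² ≈ 119.8, rounded up to 120. This matches the stated 120.

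Inflation for 30% loss: 120 / 0.7 = 171.4, so 172, against 170 stated, which is close enough. Conversely, 170 × 0.7 = 119 per arm, with power 79.7%. The design therefore counts on about 119 observed participants per arm at 72 weeks.

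**2. How many the definition could exclude.** 340 × 0.30 = 102. This is a ceiling at the planned rate, reached only if no drop-out has a qualifying SFQ. If an earlier SFQ qualifies, the number is smaller. For example, 10% without any qualifying SFQ is 34 and 15% is 51 (both shares assumed).

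**3. What exclusion could do to the estimate.** The article gives no arm-specific loss and nothing about unobserved outcomes, so these inputs are assumptions. Let the observed benefit be 2 points, let d_P and d_T be the proportions unobserved in PEPS and in treatment as usual (TAU), and let unobserved participants score s points worse than observed participants in the same arm.

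Same shift in both arms: all-randomised benefit = 2 − (d_P − d_T) × s.
Shift in PEPS only: all-randomised benefit = 2 − d_P × s.

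| Assumed loss PEPS / TAU | Who is shifted | s = 1 | s = 2 | s = 3 |
|---|---|---|---|---|
| 30% / 30% | both arms alike | 2.0 | 2.0 | 2.0 |
| 35% / 25% | both arms alike | 1.9 | 1.8 | 1.7 |
| 40% / 20% | both arms alike | 1.8 | 1.6 | 1.4 |
| 30% / 30% | PEPS only | 1.7 | 1.4 | 1.1 |

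If TAU loses more, or if those lost would have done better, the sign reverses. For scale, the standard error of the difference at 119 per arm is 4.53 × √(2/119) = 0.587.

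**4. Power.** With 240 × 0 change in total loss, only the split moves: power is 79.7% at 30/30, 79.4% at 35/25 and 78.7% at 40/20. The issue is bias, not power.

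**The case against.** The strongest reply is that the definition is printed openly, so a reader can see who is left out, and that sets of this kind are common. The set also imposes no treatment condition: a PEPS participant who gives up waiting for a group but completes an SFQ stays in. Both points are fair. They limit the harm but do not make the label correct.

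A reader might infer from the Discussion that part of the 30% is loss specific to PEPS. The article does not support that. The window it describes opens at consent, and the aggravating factor it names is assessment before randomisation, which falls on both arms and cannot affect a randomised set. Nothing says that this loss comes after randomisation, is confined to PEPS, forms part of the 30%, or means a missing SFQ. What stands is plausibility: only PEPS participants wait for a group.

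A reader might also infer that record-check data exist for everyone. The Record Check section ties collection to the time a participant remains involved in the trial and does not say whether records are reviewed after withdrawal. The claim must be limited to participants for whom those data are held.

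A further objection is that an all-randomised likelihood model would not repair the worst scenarios in the table. That is correct. Such a model assumes data missing at random, and people with only a baseline SFQ add almost nothing to the estimated 72-week difference. Only a sensitivity analysis that departs from that assumption addresses those rows. Finally, the article's silence on a missing-data method is no fault, since that commonly belongs to the analysis plan.

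**Conclusion.** The point holds in a limited form. The efficacy set conditions on an observed post-randomisation outcome, so it should not be called intention-to-treat, and the qualifying visit is not fixed. Taken literally, the same rule needlessly ties record-based and referrer-rated outcomes to SFQ response. That follows from the text and needs no assumption.

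The numerical consequence is uncertain in size and direction. At most 102 of 340 are affected at the planned loss. An observed 2-point benefit corresponds to 2.0 in all randomised if loss and shift are equal in both arms, to 1.9 to 1.4 under the assumed differential losses, and to 1.1 in the least favourable row shown. These are illustrations. They do not show that the trial will overstate PEPS. They matter because 2 points is both the powered difference and the article's threshold for clinically significant change, so a modest shift could alter the reading of the result.

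**What to change.** 1. Define the primary population as all randomised participants by allocated arm, using every available SFQ under a stated missing-at-random approach.
2. Add a sensitivity analysis that covers all randomised participants and lets unobserved outcomes depart from missing-at-random by different amounts in each arm.
3. Rename the present set available-case or modified ITT, state which SFQ visit qualifies, and keep it as supportive.
4. Analyse record-check service use and referrer-rated GAF on all randomised participants who have those data, whether or not an SFQ was returned.

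The cost is wording and modest programming, settled before unblinding. Extending record review to people who have withdrawn is not part of this proposal. The downside is some extra analysis and possibly a less favourable estimate.
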